#### Data analysis

Data will be summarised using univariate statistics (number, mean, standard deviation, median) or frequency (number, percentage). For baseline characteristics, between-group comparisons will be performed with the χ2 test for categorical variables and two-sample *t*-tests for continuous variables. The primary time-point for effectiveness analyses on improvement of QoL is 12 months. Change in the KCCQ-OS from baseline to 12 months will be compared between the intervention and standard care groups. Additionally, a linear mixed-effects model will be used to compare change in the KCCQ-OS over time between the randomly allocated treatment groups to account for missing data and longitudinal trends. The effect of CardioMEMS in comparison to standard care in changes of KCCQ clinical summary and KCCQ-OS scores is compared using repeated measurement analysis of covariance adjusted for baseline KCCQ score. EQ-5D-5L scores will be analysed in a comparable manner. The secondary endpoint in the study is the number of HF hospitalisations during follow-up. A Cox proportional hazard regression model with Anderson-Gill method for recurrent events will be used for analysis of clinical events (HF hospitalisations, mortality rates). Additionally, Cox proportional hazard models are implemented to analyse time to first events, including mortality and hospitalisation. Hospitalisation rates and mortality rates are estimated using the Kaplan-Meier method, and *p*-values are computed using the log-rank test. All reported analyses are performed using the intention-to-treat principle. All statistical tests will be 2‑sided with a significance level of 0.05.

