## Methods

### Study design

The MONITOR HF trial is an investigator-initiated, multicentre, randomised clinical trial enrolling 340 patients with chronic HF NYHA class III and at least one HF hospitalisation in the previous 12 months. In total, 20 Dutch hospitals, distributed over the country, agreed to participate (Fig. 1; Electronic Supplementary Material, Appendix Tab. 1). Sites without previous experience with CardioMEMS will go through a learning curve of two patients for sensor implantation and pressure management, who do not participate in the main trial but are followed according to study protocol. Alternatively, added centres can proctor two patients in an experienced centre. The MONITOR HF trial aims to test the effect of PA monitoring in addition to standard HF care on quality of life (QoL), the number of HF hospitalisations and cost-effectiveness in a Dutch health care system. Four populations for analysis are defined in the MONITOR HF trial: intention-to-treat, as-treated and per-protocol (time until implant after randomisation (maximum 3 weeks per protocol)) and safety analysis. The principal analysis for the primary effectiveness endpoint will be performed in the intention-to-treat population.

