#### Duration of follow-up

All patients will be followed for at least 12 months, resulting in a minimum follow-up of 12 months (for the last patient included) and a maximum follow-up of 36 months (for the first patient included) according to the above-mentioned enrolment schedule. The follow-up visits are scheduled at 3, 6, and 12 months and every 6 months thereafter (Fig. 3).

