### Statistical analysis

#### Sample size

The conditional coverage agencies requested 90% power on QoL endpoints and at least 85% for the secondary endpoint HF admissions in order to have adequate estimates of effect sizes for cost-effectiveness analyses (which are dependent on this set of variables). We decided to aim for 90% statistical power to detect an at least 6‑point difference in KCCQ overall summary (KCCQ-OS) score between randomised treatment groups [27]; we calculated, at an alpha level of 0.05 and standard deviation (SD) of 15, group sizes of *N*_1_ 133 and *N*_2_ 133 patients (total sample size 266 patients). With an anticipated 10% withdrawal rate, we will need to include 292 patients in total. For the secondary endpoint of HF admissions, we used two assumptions of estimated treatment effect size and estimated event rates of HF hospitalisations in the Netherlands. The long-term results of the CHAMPION trial, more comparable to our follow-up length, showed a reduction of 33% in HF hospitalisations compared to controls (182 HF hospitalisations vs 279 HF hospitalisations, in 270 and 280 patients treated with CardioMEMS vs standard care, respectively; average follow-up 18 months) and the Dutch COACH trial provided an event rate of 2.03% per month in a comparable but slightly less sick cohort of chronic HF patients [16, 17, 29]. Under these assumptions, at least 85% statistical power at an alpha level of 0.05, and a treatment effect size of CardioMEMS of 33% and event rate of 2.0% per month in the control group, when *N*_1_ 164 and *N*_2_ 164 patients, a total of 328 patients is to be included. For the secondary endpoint, EQ-5D-5L improvement in health status, 90% statistical power to detect a significant difference of 0.06 at an alpha level of 0.05 and SD 0.18, a sample size of *N*_1_ 155 and *N*_2_ 155 totalling 310 patients is needed, and by including a 10% early withdrawal rate a total sample size of 340 patients is to be included. Therefore, the total sample size of the trial required to adequately answer the research questions is 340 patients.

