#### Cost-effectiveness analysis

The cost-effectiveness analyses will be conducted in accordance with the Dutch guidelines for HTA and will calculate incremental-cost-effectiveness ratio (ICER) per quality-adjusted-life-year (QALY) gained both from a societal as well as health care perspective. For cost-effectiveness analyses, the EQ-5D-5L is the required standard tool to use. In addition, iMCQ, a generic instrument for measuring medical costs [26], will be used together with costs from the Dutch costing manual [28]. Cost-effectiveness will be evaluated by use of a decision analytical model, e.g. a Markov cohort simulation, developed to capture the clinical events and costs for the current and a (hypothetical) cohort of patients. The number of states (e.g. alive or dead; NYHA class; hospitalised; after a cardiovascular event) and transitions between these states distinguished in the cost-effectiveness model will be chosen based upon the available evidence regarding the natural history of disease and treatment pathways. Survival probabilities beyond the trial period can be estimated by fitting a parametric survival model to the trial data. For patients who are alive, the period of survival can be weighted by patients’ utility measured with the EQ-5D-5L. Similarly, the out-of-hospital period will be weighted by patient utility EQ-5D-5L. Missing data in the EQ-5D-5L questionnaires can be adjusted for using linear effect models or multiple imputations. Costs evaluated in the model included those for sensor implantation and device, care, HF hospitalisation, medication changes, number of visits, and end-of-life support for those who died. To extrapolate costs beyond follow-up, we will make use of standardised estimates of health-care spending from the Netherlands [30]. Total costs and QALYs will be modelled according to the time (in intervals) patients spent in each health state. The ICER will be evaluated against the appropriate severity-weighted threshold for cost-effectiveness.

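### Kaplan-Meier curves for hospitalisation, with deaths censored, overstate the proportion of patients hospitalised; cumulative incidence should be reported instead

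*Protocol article*

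**What the plan says.** The Data analysis section names three tools for clinical events.

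- **Recurrent events:** "A Cox proportional hazard regression model with Anderson-Gill method for recurrent events will be used for analysis of clinical events". The count of HF admissions, a secondary endpoint, falls here.
- **First events:** "Cox proportional hazard models are implemented to analyse time to first events, including mortality and hospitalisation".
- **Absolute rates:** "Hospitalisation rates and mortality rates are estimated using the Kaplan-Meier method", with p-values from the log-rank test.

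No section of the article names a cumulative incidence function or another competing-risk estimator, or says how a death enters the hospitalisation curve. The Secondary endpoints section lists all-cause and cardiovascular mortality among the other endpoints.

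The population is "patients with chronic HF NYHA class III and at least one HF hospitalisation in the previous 12 months" (Study design). The Duration of follow-up section gives "a minimum follow-up of 12 months (for the last patient included) and a maximum follow-up of 36 months (for the first patient included". For the HF admission endpoint, the Sample size section assumes an "event rate of 2.0% per month in the control group" and "a treatment effect size of CardioMEMS of 33" per cent. No mortality rate is stated anywhere.

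**The concern.** A patient who has died cannot be admitted later. A Kaplan-Meier curve for first hospitalisation has no place for death, so deaths are ordinarily entered as censored observations. One minus that curve then describes the risk of admission if death were removed. It does not describe the share of randomised patients who are admitted. The first quantity is at least as large as the second, and strictly larger once deaths occur among patients not yet admitted.

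The same reasoning applies to cardiovascular mortality if deaths from other causes are censored.

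At stake are the absolute percentages hospitalised in each arm and the absolute difference between them. Readers will take these as what happened to patients. The gap grows with follow-up, and the patients are in NYHA class III with a recent admission, followed for one to three years.

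**Working it through.** The article reports no Kaplan-Meier probability, so there is no figure of its own to reproduce. The check compares what the two estimators target.

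**Inputs**
- Control hazard h = 0.020 per month, from the Sample size section. The article calls this an event rate; reading it as a constant first-admission hazard is an assumption.
- Intervention hazard 0.020 × (1 − 0.33) = 0.0134 per month, from the same section.
- Horizons of 12 and 24 months. Every patient is planned to reach 12. With steady inclusion over 24 months, planned follow-up runs evenly from 12 to 36 months and averages (12 + 36)/2 = 24.
- Annual mortality m is **assumed**, 5% to 25%, equal in both arms. The monthly death hazard is μ = −ln(1 − m)/12: 0.00427 at 5%, 0.00878 at 10%, 0.01860 at 20%, 0.02397 at 25%.

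**Formulas**
- One minus Kaplan-Meier, deaths censored: 1 − exp(−hT).
- Proportion actually hospitalised (cumulative incidence): h/(h + μ) × [1 − exp(−(h + μ)T)].

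**Worked case:** control arm, 24 months, m = 10%
- Kaplan-Meier: 1 − exp(−0.48) = 38.1%.
- Cumulative incidence: 0.020/0.02878 × [1 − exp(−0.6907)] = 34.7%.
- Excess: 3.5 points (unrounded 3.46).

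**Control arm**

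| Horizon | 1 − KM | Actual at m = 5% | 10% | 20% | 25% | Excess (points) |
|---|---|---|---|---|---|---|
| 12 months | 21.3% | 20.8% | 20.3% | 19.2% | 18.6% | 0.5 to 2.7 |
| 24 months | 38.1% | 36.4% | 34.7% | 31.3% | 29.7% | 1.7 to 8.5 |

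**Difference between arms at 24 months** (from unrounded values)
- Kaplan-Meier: 38.1% − 27.5% = 10.6 points.
- Cumulative incidence, m = 10%: 34.66% − 24.94% = 9.7 points.
- Cumulative incidence, m = 20%: 31.30% − 22.45% = 8.8 points (8.849 before rounding).

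**Risk ratio at 24 months:** 0.72 by either estimator at both 10% and 20% mortality (27.5/38.1; 24.94/34.66; 22.45/31.30).

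At 36 months the control-arm gap would be larger: 51.3% by Kaplan-Meier against 48.0% at 5% mortality and 36.1% at 25%. Only the first patients included are planned to be followed that long, so this is an extreme and not a typical figure.

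**The case against.** The strongest case against the point is that it concerns descriptive curves only. The Kaplan-Meier sentence follows the sentence on time to first event and reads as its companion. The primary KCCQ analysis does not use it. Log-rank and Cox tests with deaths censored are valid comparisons of the cause-specific hazard. Other listed endpoints bring death in, such as the composite of death with HF admissions and the days alive and out of hospital. This is also a condensed article, and the treatment of deaths in the curves could be set out in an analysis plan that is not shown. All of this stands and limits the weight of the point. It does not remove it, because the article itself fixes Kaplan-Meier for hospitalisation and names no other estimator of absolute risk.

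Two stronger readings are tempting.

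- **The cost-effectiveness model inherits the error.** A reader might infer this because the Cost-effectiveness analysis section speaks of "transitions between these states distinguished in the cost-effectiveness model". That section does not say that Kaplan-Meier estimates are used as inputs. In a Markov model with its own transition to death, the suitable input for admission is the cause-specific hazard, which a death-censored curve reflects. Entering cumulative incidence beside a death transition would count death twice.
- **The number of admissions is analysed as a first event only.** The plan gives that endpoint to the Andersen-Gill model, so this does not hold.

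**Conclusion.** The point holds as a modest correction to how absolute hospitalisation risk is estimated. The direction of the bias within each arm is certain if deaths are censored, and does not depend on the mortality rate. That deaths would be censored is inferred from ordinary practice.

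The size depends on constant hazards, on reading 2.0% per month as a first-admission hazard, and on assumed mortality, since the article gives none. The widening of the arm difference also assumes equal mortality in the two arms. Under these assumptions the bias is small at 12 months and becomes material at 24 months if mortality is in the middle or upper part of the range.

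No hypothesis test, hazard ratio or primary result changes. The documents do not support extending the point to the cost-effectiveness model.

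**What to change.** - Report Aalen-Johansen cumulative incidence for first HF hospitalisation, with death as the competing event, and for cardiovascular death, with other death as the competing event.
- Optionally add the mean cumulative number of HF hospitalisations with death as a terminal event (Ghosh-Lin), as the absolute companion to the Andersen-Gill model.
- Keep Kaplan-Meier for all-cause mortality and for composites that include all-cause death.
- Keep log-rank and Cox for hospitalisation, labelled as cause-specific comparisons.

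The cost is a change of analysis wording and the use of standard software, with no new data and no change in sample size. The reported hospitalisation percentages will be somewhat lower than Kaplan-Meier would have given.

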#### Cost-effectiveness analysis

The cost-effectiveness analyses will be conducted in accordance with the Dutch guidelines for HTA and will calculate incremental-cost-effectiveness ratio (ICER) per quality-adjusted-life-year (QALY) gained both from a societal as well as health care perspective. For cost-effectiveness analyses, the EQ-5D-5L is the required standard tool to use. In addition, iMCQ, a generic instrument for measuring medical costs [26], will be used together with costs from the Dutch costing manual [28]. Cost-effectiveness will be evaluated by use of a decision analytical model, e.g. a Markov cohort simulation, developed to capture the clinical events and costs for the current and a (hypothetical) cohort of patients. The number of states (e.g. alive or dead; NYHA class; hospitalised; after a cardiovascular event) and transitions between these states distinguished in the cost-effectiveness model will be chosen based upon the available evidence regarding the natural history of disease and treatment pathways. Survival probabilities beyond the trial period can be estimated by fitting a parametric survival model to the trial data. For patients who are alive, the period of survival can be weighted by patients’ utility measured with the EQ-5D-5L. Similarly, the out-of-hospital period will be weighted by patient utility EQ-5D-5L. Missing data in the EQ-5D-5L questionnaires can be adjusted for using linear effect models or multiple imputations. Costs evaluated in the model included those for sensor implantation and device, care, HF hospitalisation, medication changes, number of visits, and end-of-life support for those who died. To extrapolate costs beyond follow-up, we will make use of standardised estimates of health-care spending from the Netherlands [30]. Total costs and QALYs will be modelled according to the time (in intervals) patients spent in each health state. The ICER will be evaluated against the appropriate severity-weighted threshold for cost-effectiveness.

### Trial structure, registration and organisation

The MONITOR HF trial is designed, implemented and overseen by an independent executive board and steering committee. The study was evaluated by scientific committees (ZonMW) and councils of the National Health Care Institute and patient councils. Site and data management is performed by the CRO Erasmus MC trial organisation. An independent data safety monitoring board (DSMB) has been established and will review safety data on an ongoing basis during the trial in accordance with the DSMB charter. An independent clinical endpoint committee (CEC) has been established, blinded to study group assignment, and will review and adjudicate all deaths and hospitalisations using prospectively defined criteria in the CEC charter. The adjudicated data are used for outcomes regarding hospitalisations and deaths. The DSMB and CEC are organised and led by an external independent organisation (Cardialysis, Clinical Trial Research Centre). The clinical trial is structurally monitored by independent monitors from the research trial organisation. The study complies with good clinical practice in accordance with the Declaration of Helsinki and the laws and regulations applicable in the Netherlands, including the European Union General Data Protection Regulations, as the clinical trial has been approved by the appropriate medical ethics committee and review board (Erasmus MC, MEC 2018-1563). The clinical trial was registered under the number NL7430 (NTR7672, clinical trial registration number) on 12 December 2018. The study started enrolment on 1 April 2019.

## Discussion

This multicentre, randomised clinical trial (MONITOR HF) will evaluate the efficacy and cost-effectiveness of remote PA monitoring with CardioMEMS applied in addition to standard care in patients with chronic HF, from a European perspective. The benefits of remote monitoring with CardioMEMS were demonstrated in the CHAMPION trial of 550 participants in the US, who were studied between 2007 and 2009 [14], and have been confirmed in several large-scale post-marketing registries [15–17]. The MONITOR HF trial will provide contemporary trial data on the effectiveness of CardioMEMS in a highly organised European health care system where HF patients are routinely followed in dedicated HF outpatient clinics after an HF admission. The recently published CHAMP-HF and CHECK-HF registries highlight the differences in guideline adherences between the Netherlands and the USA [3–5]. Additionally, profound differences exist between Europe and the USA as regards the organisation of health care as well as financial structures. The current study will provide the individual data necessary to perform calculations on cost-effectiveness of remote monitoring from a European health care perspective.

In the CHAMPION trial, QoL was not a primary endpoint and data are only available on small subsets of patients with a short follow-up [16]. The current trial has QoL as a primary endpoint, which is a novel aspect in telemonitoring but is emerging as a relevant clinical endpoint in HF trials. Additionally, QoL might hypothetically be valued most by the patient, as living longer in poor health might not be the main focus of choice. For the secondary endpoint, the number of HF hospitalisations, it is most likely that rehospitalisation rates differ between the USA and Europe, and we expect a lower event rate in the Dutch health care system with dedicated HF nurses and HF outpatient clinics as the organisation of standard care differs [29]. Dedicated HF outpatient clinics and structured HF care after HF admissions are emerging throughout Europe as standard HF care, including multidisciplinary team approaches, heart teams, and cardiac rehabilitation programmes as advocated in the 2016 ESC guidelines [23]. The recently published US Post Approval Study (PAS) confirms the consistent treatment benefit with CardioMEMS in chronic HF patients, reducing the number of HF hospitalisations in a more contemporary setting [20]. However, the patients included in the PAS study were their own historical controls and no randomised comparison to standard care without PA monitoring was made. However, the main inference of the PAS is the consistent safety of the implantation procedure and the durability of the sensor without sensor failures [20].

From a financial point of view, a cost-effectiveness analysis using the US CHAMPION trial data calculated an ICER for costs per QALYs of $29,593 for CardioMEMS based on US health care data [21]. Extrapolating the US data to European health care systems, such as those in the UK, the Netherlands and Germany, showed that PA-pressure-guided HF therapy is anticipated to be cost-effective, but the intervention increases costs compared with usual care by £10,916 over a time horizon of 10 years while the ICER is estimated to be £19,274 with a reduction in admissions [22]. The analysis did not include staff time, due to a lack of data concerning this variable. Running the model with estimated staff time included resulted in an increased ICER of between £22,342 and £25,464 per QALY gained [22]. No individual data from European systems are currently available.

### Other forms of telemonitoring and available evidence

Several studies have been performed using non-haemodynamic parameters of remote monitoring such as signs and symptoms of HF, blood pressure or daily weights. These studies have shown no effect on HF hospitalisations [6–15]. Clearly, simple markers such as weight or blood pressure are inadequate for monitoring fluid status and if the variation in weight is caused by decompensation, treatment comes too late and cannot prevent a hospitalisation. Additionally, some studies have investigated natriuretic peptides to guide HF therapy, but these were not successful in reducing HF hospitalisations [10]. Other studies with non-haemodynamic parameters of remote monitoring have focused on information from ICD devices using intrathoracic impedance or other specific combinations of parameters in algorithms [13–15]. None of these studies have shown any actual benefit in reducing the number of hospitalisations. Most recently, the TIM-HF 2 trial was one of the first studies to show a small benefit of remote monitoring in HF patients with regard to length of hospital stay, despite its labour intensity (fully staffed telemedicine centre)[11].

The 2016 ESC guidelines report on the lack of consistent evidence for non-haemodynamic telemonitoring or remote monitoring in HF patients. The guidelines state that remote monitoring may be considered in selected patients to improve HF outcome with individual approaches such as CardioMEMS to reduce the risk of HF admissions and multi-parameter monitoring with ICD (in-time approach) to improve outcome in HFrEF with a level IIb class B recommendation [23].

